## Female HIV Acquisition*.*

Information on women will be derived from the RCSS surveillance surveys, and women are not enrolled in the male circumcision trials. Female HIV acquisition associated with the male partner’s circumcision status will be assessed among HIV-negative women in relationships with HIV-positive men. Please note, we do not enroll HIV-discordant couples; the men are individually enrolled in the circumcision trials and the women individually enrolled in the RCSS. Couples linkage will only be done retrospectively after completion of the trials, although promotion of couples VCT will be ongoing throughout the study. The information on male partner circumcision and HIV status will be derived from this retrospective linkage.

Our observational data in HIV-discordant couples found a male-to-female transmission incidence of 5.2/100 py if the male was circumcised and 13.2/100py if the male was uncircumcised (RR = 0.39). (Please note, we strongly promote condoms and couples counseling, but acceptance of these services within married couples is low). We estimate sample sizes required to detect an efficacy of this magnitude, with  = 0.05 and 1- = 0.80. The person years accrued for female exposure in discordant couples with an HIV+ male partner can be estimated from the number of prevalent and incident discordant couples with HIV+ men, as follows:

***i.*** *Person years contributed by prevalent HIV+positive men in discordant relationships with HIV- negative women:* We estimate that 500 HIV positive males per arm will accept enrollment . From prior data, 80% of men can be linked to a female partner and 55% of prevalent HIVpositive men have HIV-negative female partners. Thus we expect 220 HIV prevalent males in a discordant relationship (i.e., 500 x 0.8 x 0.55). Assuming

85% annual follow up, we estimate that 220 HIV-discordant, male HIV+/female HIV- couples, will provide 186 py in the 1st follow up year and 158 py in the 2nd follow up year, yielding a total of 344 person years in exposed, initially HIV- women. With 344 py per arm, will have 85% power to detect a RR = 0.39. Assuming 7.5% contamination, the sample size is sufficient to detect a RR* of 0.41 with 80% power.

***ii. Sample size for female acquisition after stratification by male HIV viral load*:**

We observed no seroconversions among women if their HIV+ male partner’s viral load was below 50,000 copies per mL and the HIV-positive male was circumcised, whereas among couples with HIV-infected uncircumcised men, the incidence rate was 9.6/100 py. Thus, stratifying by the viral load of HIV-positive males we will be able to detect an effect of this magnitude with 110 py, per arm ( = 0.05 and 1- = 0.80. In our study, 87.1 % of infectedmen in discordant relationships had viral loads < 50,000 copies per mL, so in this subgroup we expect to observe ~ 239 py in each arm. Therefore, the study has 98% power to detect an effect of circumcision in men with HIV-1 viral loads <50,000 cps/mL. Since this is an *a priori* hypothesis, based on observational data, such subgroup analysis is justified.

## Behavioral disinhibition:

These estimates are based on the total populations of HIV- men enrolled in the Gates and NIH trials

From prior data we expect ~ 25% of men to have multiple sex partners, ~ 17.0% to use condoms inconsistently, ~ 5.0% to consistently use condoms, ~ 46.0% report alcohol consumption in the previous 7 days and ~42% report alcohol consumption with sex. These behaviors have been shown to be significantly associated with HIV risk in the Rakai population. Assuming these rates pertain in the control arm, we will have 80% power to detect the following markers of behavioral disinhibition in the intervention arm: a) an increase in multiple sex partners to 30%, b) a reduction of inconsistent condom use to 13.2%, and c) a reduction in consistent condom use to 3% (i.e., an overall reduction in condom use of - 5.8%), and d) and an increase in alcohol use within the past 7 days to 50.4%, or of alcohol consumption with sex to 46.4%.

We will also assess behaviors among the ~1000 men who decline VCT, compared to the men who accept VCT, to determine whether VCT acceptance is associated with lower risk behaviors.

## Accrual and Feasibility:

The average number of men aged 15-49 per community is ~ 190, of whom we expect 137 to be uncircumcised and HIV-negative (84% uncircumcised and 86% HIV-).2 Assuming 50% acceptance of circumcision we expect an average of 69 subjects enrolled per community. We enrolled male participants from RCSS communities and allowed non-cohort participants to enroll as “walk in subjects”. We believed that the current cohort surveillance participants and walk in participants will readily achieve the sample size goals. (Our previous trials enrolled over 12,000 subjects).

***Feasibility of follow up:***

In the present trial, the eligibility criteria include intent to remain in the community for at least one year. We will implement additional procedures for active tracing. In brief, we will a) ask relatives of absent subjects to contact them or to provide contact addresses, b) ask absentees to return for follow up and compensate them for time and travel expenses, and c) establish peripheral hubs in urban centers such as Masaka and Kampala where most absentees go for work or education, in order to facilitate follow up outside the District. With eligibility based on intent to stay and active tracing, we believe that we can achieve a minimum of 85% or more follow up. In our maternal-infant trial we achieved 94% follow up of 4,036 persons, and in our MER study we have achieved 95.4% follow up on a sample of 383 subjects. We therefore believed follow up of 85% was feasible in the proposed trial.

## Randomization and Stratification

- Johns Hopkins generated a list of randomized numbers in blocks of 20 to insure comparability of men randomized to intervention and control arms, within cohort communities or group of “walk in” participants”.

- A random assignment sheet was placed in an opaque sealed envelope. The envelopes in blocks of 20, were generated by Rakai Health Sciences Program Data management using a computerized list provided by JHU, and were retained securely by the Circumcision Data Management Team.

- After enrollment and consent, men were asked to select an envelope from the block of 20 envelopes being used at that time. The envelope contained the assignment sheet showing the randomization number and random assignment to treatment or control arm. The Enrollment Team then affixed the label with the individual’s study ID number to the sheet. (Form 18).

- The assignment sheet with the study ID# labeled was entered into a data base to record study arm allocation.

- The list of random allocation numbers linked to participants was retained at JHU in locked files, and in password protected computers.

- All randomization envelopes were logged out and in daily. A data base monitored used and unused allocation numbers, and tracked disposition of all envelopes.

- Men were randomized at the enrollment visit. If, participants change their minds and withdrew, or at a subsequent preoperative visit, the surgeon determined that circumcision was contraindicated for medical reasons, the men were considered enrolled and randomized.

## Analysis Plan

### Primary Endpoint, HIV incidence in Males.

This analysis will be done separately for HIV-negative men enrolled in the Gates and NIH trials, and for the combined population of HIV-negative males enrolled in both trials.

HIV incidence per 100 person-years (PY) will be estimated, assuming seroconversion occurred at the mid-point of each follow up interval. In both arms, time from enrollment will be accumulated up to 24 months of follow up. Person time will discount the postoperative period of sexual abstinence for intervention arm subjects. Baseline samples of subjects who seroconvert during the first follow up interval will be tested by detuned EIA and PCR to detect prevalent infections during the window period, and any suspected prevalent cases will be excluded from incidence analyses.

Exploratory data analysis will examine the populations in the two arms at enrollment to assess baseline comparability. HIV incidence will be determined by strata of covariates such as age, marital status, behaviors (e.g., number of partners, condom use), health status and other variables to identify potential confounders. We will also assess contamination (i.e., cross-over) among men allocated to circumcision who do not receive surgery, and among control subjects who opt to have circumcisions performed from non-Project services.

An intent-to-treat approach will be taken, and all men who enroll will be included, irrespective of whether intervention arm participants ultimately receive circumcision, or whether control arm participants crossover and receive circumcision prior to 24 months follow up. The rationale is that a proportion of enrolled men who initially accept circumcision may change their mind prior to receipt of surgery, and such men are likely to be self-selected. Because circumcision is delayed in the control arm, such self-selection could be differential between randomization groups. Therefore, in the circumcision arm, enrolled men who subsequently refuse circumcision, will be ascribed half the person time from enrollment to scheduled date of circumcision.

We will assess HIV incidence in enrolled HIV-negative men. The primary analytical model that will be used will be Poisson regression to compare the HIV incidence rates between the two study arms.113 The relative incidence of HIV in the circumcision arm versus the control arm, will be estimated using Poisson regression models with adjustment for individual-level variables found to differ between groups at enrollment, and for potential confounding variables. Potential confounders determined from prior risk analyses will include age, marital status, risk behaviors (i.e, number and nature of partners, condom use and alcohol use), or imbalance of covariates between study arms will be used for adjustment in the primary models. Secondary analyses will include any additional potential confounders identified during exploratory data analysis and will include covariates associated with HIV incidence (p < 0.15), or covariates with an incidence RR > 2.0. Poisson multivariate models will be fit for the whole population and for strata of particular interest (e.g., by age, sexual risk behaviors etc.). Although we are doing an individually randomized trial, the structure and logistics of field work requires that men be randomized within communities. Thus, we will also fit Poisson models with random effect terms for each community, to insure adjustment for clustering in HIV incidence.

We will also assess the associations between selected STDs and STD symptoms and incident HIV infection to determine whether effects of circumcision on HIV incidence may be mediated by STD cofactors. If, as expected from prior analyses, selected STDs and STD symptoms such as GUD are associated with incident HIV, we will assess the circumcision effects on HIV incidence using stratified models or via interaction terms.

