# STUDY TREATMENTS AND PROCEDURES AFTER CLOSURE OF ENROLLMENT

## Surgery

## 6.1a Trial

On the scheduled day of surgery transport was provided if needed. Men who previously consented but changed their minds and were contactable were interviewed to ascertain why they declined surgery. Repeat visits to contact absentees were conducted for a period of approximately one month, and if not contacted, their location and reason for absence were obtained from household members. Men who reported for surgery more than 30 days since last hemoglobin test had a repeat hemoglobin test. Men who changed their minds or who had a medical contraindication resulting in delayed surgery can could come for surgery within 6 months post enrollment. If at 6 months a man randomized to circumcision decided not to have surgery, he was classified as a cross-over and followed over two years**.** If a man had a contraindication that did not resolveby 6 months, he was **classified as not eligible and withdrawn from the study.**

For men who received delayed surgery between 1-6 months, the subsequent 6, 12 and 24 months visits were scheduled from time of surgery rather than from time of enrollment. For men with surgery delayed for less than 1 month (<1month), subsequent 6, 12, and 24 month follow up occured from time of enrollment.

Men were re-consented for surgery (Surgical Consent Form III), and if they agreed to surgery they were briefly interviewed and examined by a clinical assistant, and by a physician who certified fitness for surgery (Preoperative Interview/Exam Form 03).

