### Female HIV Acquisition

We propose an intent-to-treat analysis . The unit of analysis is women in relationships with HIV-positive male partners. Although the male’s circumcision status can be ascertained by interview with the female partner, the male’s HIV status can only be determined by linking couples from within the RCSS. This will be done at the conclusion of follow up. The linkage will allow identification of men enrolled in the circumcision trials, determine their randomization arm and their HIV status, and provide an objective measure of circumcision status as well as the timing of the circumcision.

We will determine male-to-female transmission (female HIV incidence per 100 py) in the circumcision arm relative to control using multivariate Poisson regression as described for male HIV acquisition in 8.9.a above.

Data are also collected on the frequency of intercourse, so in addition, we will estimate the probability of HIV infection per coital act among circumcised and non-circumcised men using published methods.20,116 The probability of transmission in the ith couple (Pi) can be written as 1- (1-) n i, where ni is the number of acts during the follow up period, and the infectivity () is the probability of transmission per act.116 Allowing the infectivity to depend on covariates through a complementary log-log link, leads to the regression model [log -log (1-P)] = log ni + b0 + b1X1 where b1 and X1 are vectors of regression coefficients andcovariates, respectively. This model will be fit using statistical methods for generalized linear models, specifically binomial regression with a complementary log-log link and offset term log ni (SAS Institute Inc., Cary, NC.). The comparisons will again be between circumcision arm and control. We have shown that the probability of male-to-female HIV transmission per coital act is 0.0004 if the malepartner was circumcised and 0.0015 if the male was uncircumcised (RR = 0.27, unpublished).

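### Section 8.8.1 removes postoperative abstinence time from the intervention arm only, which does not fit its intent-to-treat approach and raises that arm's rate by about 3–6%; late visits after delayed surgery are not reconciled with the 24-month limit

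*Protocol*

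**What the plan says.** Section 8.8.1 of the protocol (Primary Endpoint, HIV incidence in Males) first sets a common clock: "In both arms, time from enrollment will be accumulated up to 24 months of follow up". The next sentence makes an exception for one arm: "Person time will discount the postoperative period of sexual abstinence for intervention arm subjects". The section gives no start, end or data source for the abstinence period, and does not say whether infections acquired in it are counted. Infections are dated by "assuming seroconversion occurred at the mid-point of each follow up interval". The same section declares an intent-to-treat approach that includes every enrolled man whatever surgery he receives. A second rule also applies to the circumcision arm alone: men who refuse surgery "will be ascribed half the person time from enrollment to scheduled date of circumcision".

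Section 6.1a (Trial, under Surgery) fixes the visits. "For men who received delayed surgery between 1-6 months, the subsequent 6, 12 and 24 months visits were scheduled from time of surgery". Where surgery was delayed by less than a month, "subsequent 6, 12, and 24 month follow up occured from time of enrollment". No restart is given for controls.

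Section 8.8.2 (Female HIV Acquisition) compares the arms "using multivariate Poisson regression as described for male HIV acquisition in 8.9.a above". In the protocol's contents list, 8.9 is interim monitoring and the male analysis is 8.8.1, so the cross-reference does not resolve as printed.

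**The concern.** Abstinence after surgery is caused by the assignment. Removing it from one arm's denominator, while controls keep all their time, abstinent or not, gives the two arms different time bases. The comparison is then no longer the plain randomized one that intent-to-treat implies. If infections in the removed time stay in the numerator, the intervention-arm rate can only go up. If they were dropped as well, infections acquired before healing would disappear, and the section on potential risks names intercourse before healing as a possible cause of HIV acquisition.

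The visit rule raises a separate question. Men with delayed surgery are tested after the month at which person-time is meant to stop, and the plan does not say how those tests enter.

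The ambiguity matters most in 8.8.2. The protocol's background and its section on safety and programmatic considerations treat the weeks before healing as the suspected period of extra risk to female partners. How time and events in those weeks are handled should not be left to a cross-reference.

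**Working it through.** **The plan's own figures.** Section 8.2 takes 2,500 men per arm with 15% annual loss: 2,500 × (0.85 + 0.85²) = 3,931 py, against 3,932 stated. No abstinence time is deducted in either arm. A two-look Poisson simulation at 1.8/100 py, with 3,028 then 3,932 py per arm and the stated boundaries 2.303 and 2.017, gives 89.2% power at RR 0.53 (stated 89.5%) and a 5.0% type I error. The design figures therefore rest on undiscounted time in both arms.

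**Length of abstinence (assumption).** The protocol gives no number. Men are advised to wait for certified healing, and the third postoperative visit is at 3–6 weeks, with weekly visits after that if healing is incomplete. I take w = 3–6 weeks out of 104; it could be longer for slow healers.

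**Effect of the discount with events kept.** The intervention-arm rate is multiplied by 1/(1 − w/104).

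| w | Factor | Risk persists: a true 0.53 reads as | No risk: discounted RR | No risk: RR on time from enrollment |
|---|---|---|---|---|
| 3 weeks | 1/(1 − 3/104) = 1.030 | 0.53 × 1.030 = 0.546 | 0.53 | 0.53 × 101/104 = 0.515 |
| 6 weeks | 1/(1 − 6/104) = 1.061 | 0.53 × 1.061 = 0.562 | 0.53 | 0.53 × 98/104 = 0.499 |

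In both cases the discounted RR is 3–6% above the RR on time from enrollment. What differs is which of the two equals 0.53.

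**Allowing for losses.** Abstinence comes early, before most losses, so its share of accrued time is somewhat larger. With 92.5–100% of men having surgery:
- 4 weeks removes 177–192 py, or 4.5–4.9% of 3,932.
- 6 weeks removes 266–288 py, or 6.8–7.3%.
- The factor is then about 1.05–1.08, and 0.53 reads as 0.56–0.57 if risk persists.
- In the same simulation with 4.5–7% removed, events kept and risk persisting, power falls from 89% to 84–81%. Under no effect, the chance of a false finding of harm rises from 2.5% to 4.6–6.2%.

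**Visit clock.** For surgery d months after enrollment (d = 1 to 6):
- The last test falls at d + 24, that is 25–30 months.
- The last interval runs from d + 12 to d + 24, so its midpoint is d + 18, that is 19–24 months.
- The midpoint never passes 24 months. An infection that truly occurs as late as month 30 can therefore be dated inside a 24-month denominator. For these men the window for detecting infection is 25/24 to 30/24 of the intended length, or 4–25% longer.
- The share of men delayed is not given. If 5–20% were delayed by 3 months on average (an assumption), the excess for the whole arm would be 0.05 × 3/24 = 0.6% to 0.20 × 3/24 = 2.5%.

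**The case against.** The best defence is that the discounted rate answers a legitimate question: incidence per unit of sexually exposed time. The planning value of 0.53 comes from observational data on men already circumcised or not, so it contains no postoperative abstinence. If abstinent time carries no risk, the discounted analysis returns exactly 0.53. The exception also stands openly in the sentence after the common rule, so it reads as a deliberate exception and not as an oversight. This much stands. It supports keeping the discounted rate as a secondary quantity. It does not make that rate an intent-to-treat comparison, which is what the section declares.

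Four stronger readings are tempting, and the documents do not support them:
- A reader might infer that 0.53 necessarily becomes 0.55–0.56. That holds only if risk persists in the removed time. The protocol's report of early resumption of sex concerns couples with HIV-positive men and does not show how HIV-negative men behaved.
- A reader might take the first six months alone, where the removed share is much larger. The plan specifies rates over time accumulated to 24 months and no first-interval RR, so that figure would describe no planned estimate.
- A reader might infer that women's person-time is discounted. Section 8.8.2 refers to the male Poisson regression. The discount is written for intervention-arm subjects, and women are not enrolled in the trials. The text leaves the matter open and does not state a discount.
- A reader might call the visit restart a second origin for person-time. It is a scheduling rule for one subgroup, and 8.8.1 still counts from enrollment.

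**Conclusion.** The point holds in limited form. The one-arm discount is inconsistent with the stated intent-to-treat approach and, with events kept, raises the intervention-arm rate by about 3–6% under an assumed 3–6 weeks of abstinence. The shift is conservative for a benefit, would overstate harm, and would not by itself reverse an RR near 0.53. Whether it biases a true 0.53 upward, or reports 0.53 where time from enrollment would give about 0.50–0.51, depends on the risk during the removed time, which the protocol does not settle.

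The 25–30 month tests are a real gap between 6.1a and 8.8.1. Their effect cannot be sized without the share of men delayed.

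This is something that should be fixed, not a fatal flaw. The NIH trial has already closed for efficacy, and the preamble to the statistical section says the Gates men alone do not give power for an independent HIV endpoint. For the female endpoint the need is an explicit statement, not the correction of a stated error.

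**What to change.** In 8.8.1, make undiscounted time from randomization (the enrollment visit) to seroconversion, last test or 24 months, whichever comes first, the primary denominator in both arms. The half-time rule for refusers should give way to the same definition. Place each test by its actual date since randomization. Keep the abstinence-discounted rate only as a labelled sensitivity analysis, stating when the period starts and ends, its data source, and how infections within it are treated.

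In 8.8.2, state that no discount of time or events applies to the female endpoint, and correct the cross-reference.

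Reconcile 6.1a with 8.8.1 by saying how tests at 25–30 months enter an analysis limited to 24 months, and report how many men had delayed surgery.

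The cost is a change of wording, using dates already collected. Follow-up is ongoing and couples are linked only at its end, so the change can still be made. One limitation remains: men with delayed surgery have no scheduled test at 24 months from randomization, so some interval censoring persists for them.

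### The primary Poisson model adds covariates because they differ between arms at baseline, so it cannot be written down before the data are seen

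*Protocol*

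**What the plan says.** Section 8.8.1 (Primary Endpoint, HIV incidence in Males) states: "The primary analytical model that will be used will be Poisson regression to compare the HIV incidence rates between the two study arms". The rate ratio is to be estimated with "adjustment for individual-level variables found to differ between groups at enrollment" and also for potential confounders. The next sentence begins "Potential confounders determined from prior risk analyses will include age, marital status, risk behaviors", with partners, condom use and alcohol use given as the behaviours. It then runs on, after an unclear 'or', to say that "imbalance of covariates between study arms will be used for adjustment in the primary models".

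The search for differences is described as exploratory: "Exploratory data analysis will examine the populations in the two arms at enrollment to assess baseline comparability". Selection by association with HIV incidence (p < 0.15, or a rate ratio above 2.0) is kept apart: "Secondary analyses will include any additional potential confounders identified during exploratory data analysis".

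Section 8.8.2 analyses female acquisition "using multivariate Poisson regression as described for male HIV acquisition". Section 8.7 (Randomization and Stratification) says that the coordinating university "generated a list of randomized numbers in blocks of 20", applied within cohort communities or groups of walk-in participants.

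**The concern.** Men were individually randomised, so any baseline difference between the two arms is a chance difference. Whether a variable happens to differ is no guide to whether it predicts HIV acquisition, and prognosis is the reason to adjust in a randomised comparison. An imbalance criterion in the primary model means that nobody can list its terms beforehand. Section 8.8.1 also asks for separate analyses of the Gates men, the NIH men and the two combined, so the same rule could give three different primary models.

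This leaves room to choose among models. The trial is unblinded (section 8.1). Sections 1.1 and 10.7.3 report that interim reviews found non-significantly higher male-to-female transmission in the intervention arm. Fixing covariates after that point is the situation that pre-specification is meant to prevent, and the female endpoint was still in follow-up when this version was written.

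**Working it through.** **1. The plan's own design figures, as a base for the simulation.** Section 8.2 assumes 2,500 men per arm, 15% annual loss, a control rate of 1.8/100 py and a two-sided 5% test.
- Person-years per arm: 2,500 × 0.85 + 2,500 × 0.85² = 2,125 + 1,806 = 3,931 (plan: 3,932).
- Expected events at RR* 0.57: control 3,932 × 0.018 = 70.8; circumcision 70.8 × 0.57 = 40.3.
- Wald test on log RR: SE = √(1/70.8 + 1/40.3) = 0.197. Power = Φ(0.562/0.197 − 1.96) = 81.3% (plan: 80%).

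The design reproduces. None of these figures depends on the covariate rule.

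**2. How often chance would bring a variable in.** Assume k independent baseline variables and read 'differ' as p < 0.05; neither is in the protocol. The chance of at least one is 1 − 0.95^k:

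| k | Chance of at least one |
|---|---|
| 6 | 26% |
| 10 | 40% |
| 20 | 64% |

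This is the probability that the rule is triggered. It is not a bias or an error rate.

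**3. What the rule does to the male comparison.** Poisson data were simulated for 2,500 men per arm at the plan's control rate and person-years. Assumptions not in the protocol: 10 independent binary covariates, 5 prognostic with rate ratios of 1.5 to 2.0 and 5 not, and a trigger at p < 0.05. There were 4,000 runs with no effect and 1,500 at RR 0.53.

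| Model | Rejections, no effect | Power at RR 0.53 |
|---|---|---|
| Unadjusted | 4.7% | 90.1% |
| Fixed list of the 5 prognostic covariates | 4.5% | 90.5% |
| Imbalance-triggered | 4.8% | 90.5% |
| Most favourable of the three | 5.3% | – |

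The Monte Carlo standard error of the no-effect rates is about 0.35 points. A covariate was triggered in 41% of the no-effect trials. Where that happened, the rate ratio moved from the unadjusted value by a median of 1.1% (90th percentile 2.9%, maximum 6.5%).

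**4. The female comparison.** Section 8.4 plans 344 py per arm, with 13.2/100 py for uncircumcised and 5.2/100 py for circumcised partners. Expected events are 344 × 0.132 + 344 × 0.052 = 45.4 + 17.9 ≈ 63. A simulation of the same kind at 220 couples per arm, with no effect, triggered the rule in 39% of trials. The rate ratio then moved by a median of about 4% (90th percentile about 9%). The shifts are roughly three times those for men, as expected with fewer events.

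**The case against.** The strongest reply is that the primary model does have a prognostic core named in advance. A reader of the imbalance clause alone might infer that the plan adjusts only for variables that differ and ignores prognosis. Section 8.8.1 does not support that, because it names age, marital status and risk behaviours from prior risk analyses. The primary rule also looks at enrollment variables and not at HIV outcome; outcome-based screening is already confined to secondary analyses. All of this stands and limits the point to the imbalance clause.

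It may also be said that the definition of 'differ' belongs in a statistical analysis plan. That is fair, and its absence is not the complaint. The complaint is the rule that the protocol does state: imbalance selects covariates for the primary model.

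For men, much is past repair. The NIH trial was stopped for efficacy and its findings are published (section 1.3), and section 8.1 says that the Gates men alone do not give power for an independent HIV endpoint.

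For women, the premise transfers only in part. They are not themselves randomised and are linked to the men retrospectively (sections 8.4 and 8.8.2), so differences among those analysed need not be pure chance. The male-acquisition covariates also omit male viral load, which sections 8.4 and 8.8.2 treat as an a priori factor. The remedy for women must therefore differ from that for men.

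**Conclusion.** The point holds in a limited form. The primary model is part named list and part imbalance-selected additions, joined by a sentence that does not parse. The additions make the whole model unknown before the data are seen.

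A reader might infer from the 40% trigger probability that the type I error is inflated. The calculations do not show that: applied mechanically, the rule gave 4.8%, and even choosing the most favourable of three models gave 5.3%, within Monte Carlo error of 5%. In the male simulation the rate ratio moved by about 1% at the median when triggered, and by 6.5% at most. Movement is larger at the female sample size but still usually a few percent. These sizes rest on the assumed number, independence and strength of the covariates and on the p < 0.05 trigger.

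What remains is loss of pre-specification, in an unblinded trial with a known interim direction. It should be corrected because a better rule is available at almost no cost.

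**What to change.** For the male primary model:
- Delete baseline imbalance as a reason for adjustment, and rewrite the sentence containing the 'or'.
- Close the list to the covariates already named: age, marital status, number and nature of partners, condom use and alcohol use.
- Account for the randomisation grouping (community or walk-in group), for example through the community random effect that section 8.8.1 already plans.
- Report imbalance-triggered adjustment and the p < 0.15 / RR > 2.0 screen only as labelled sensitivity analyses.

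For the female model, do not simply import the male list. Fix in advance a short list suited to about 63 expected events, include male viral load, and avoid many fixed stratum terms, which would be sparse.

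The cost is protocol or analysis-plan wording, with no new data. In the male simulation the fixed list lost no power (90.5% against 90.1% unadjusted). The one small downside is that a chance imbalance in an unlisted variable is then handled only in a sensitivity analysis.
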